##### Dosage and Administration

The intervention will consist of eight VFI-RF sessions (approximately 50 min per session) delivered over 5 months. A two-week interval between sessions (Phase 2) was selected to allow mothers sufficient time to record brief everyday interactions, upload them securely to the clinician, and enable the clinician to review the material and discuss it within the research team prior to the session. All sessions will be delivered by the same trained psychologist, who works within a psychodynamic framework and has received specific training in the use of video-feedback. Participation is entirely voluntary, and participants may withdraw at any time and/or decline to take part in any specific intervention component. Pending the outcome of the study, the treatment manual will be available upon request.

### 2.2. Outcomes

#### 2.2.1. Feasibility and Acceptability

Feasibility and acceptability will be assessed using a mixed-methods approach, combining quantitative indicators with qualitative feedback from participants and service providers. Pre-specified progression criteria will be applied using a traffic-light system, as recommended in methodological guidance for pilot and feasibility trials [35,36]. Green criteria will indicate that progression to a definitive trial is feasible without major modifications, amber criteria will indicate that progression may be feasible with protocol amendments, and red criteria will indicate that progression would not be feasible without substantial redesign. Quantitative findings and qualitative feedback will be interpreted together, adopting a holistic multi-criteria approach, to inform decisions about the feasibility, acceptability, and optimization of the intervention and trial procedures (see Table 1).

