Within this framework, a preliminary single-arm feasibility study represents an appropriate first step to evaluate whether the proposed VFI-RF can be meaningfully and safely implemented in postnatal risk contexts. Before testing its efficacy in a controlled trial, it is necessary to determine whether mothers are willing to engage with a fully online video-feedback format and whether reflective work can be sustained within a remote therapeutic setting. Feasibility evidence is therefore essential to refine the intervention procedures, address potential privacy and implementation barriers, and optimize the design of a future randomized controlled trial [30].

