### 1.2. Primary Outcomes

The primary objective of this study will be to generate preliminary evidence on the feasibility and acceptability of delivering and evaluating the VFI-RF intervention for mothers at risk during the postnatal period. In line with the aims of a feasibility study, the primary outcomes focus on feasibility and acceptability indicators rather than intervention effectiveness.

Feasibility will be assessed through enrolment indicators, including the number of mothers referred, the proportion deemed eligible, and the proportion of eligible mothers who provide informed consent. Additional feasibility indicators include intervention uptake, measured as the proportion of VFI-RF sessions attended, retention at baseline and follow-up, reasons for ineligibility or withdrawal, assessment completion, and the extent of missing data on key measures.

Feasibility indicators will be calculated using predefined denominators. Specifically, the number of mothers referred will represent all mothers referred to the study by participating services or who self-refer following study advertisements. Eligibility rate will be calculated as the proportion of referred mothers meeting inclusion criteria. Consent rate will be calculated as the proportion of eligible mothers who provide informed consent. Intervention uptake will be calculated as the proportion of scheduled VFI-RF sessions attended. Retention rates will be calculated as the proportion of consented participants completing each assessment time point (T0, T1, and T2). Assessment completion rates will be calculated as the proportion of participants who complete the planned questionnaires at each assessment wave. All feasibility indicators will be reported for the overall sample and separately for each risk group (i.e., Risk Group 1: anxiety/depression; Risk Group 2: preterm birth).

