### 1.3. Secondary Outcomes

Secondary exploratory objectives include describing preliminary trajectories in maternal reflective functioning, maternal distress, perceived social support, maternal emotional bonding with the infant, and health-related quality of life in young children. These outcomes will be examined descriptively and exploratorily, with the aim of assessing the suitability and sensitivity of the selected measures for use in a future controlled trial, rather than testing intervention effectiveness.

By examining feasibility, acceptability, and preliminary clinical trajectories across different maternal risk conditions, this study will provide information on the practicality of delivering an exclusively online VFI-RF intervention during the postnatal period and on the suitability of the selected procedures and outcome measures for future randomized controlled trials (RCTs). In parallel, the study will explore potential barriers to implementation and to a subsequent larger-scale RCT, as well as determine what amendments and/or additional information may be required to optimize the design, delivery, and evaluation of the intervention in future trials. The practicality of implementing these changes will also be considered.

Overall, these findings will be used to determine whether a definitive main study is: (a) not feasible; (b) feasible pending modifications to the study protocol; or (c) feasible as originally designed.

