### 1.4. Trial Design

This multicenter study is an open-label, single-arm feasibility study using a pre–post design with a nested qualitative evaluation. The VFI-RF will be delivered synchronously online by a trained clinician. Assessments will be conducted at three time points: baseline (T0; infant age ~3 months), post-intervention (T1; infant age ~8 months), and follow-up (T2; infant age ~12 months). Qualitative data will be collected through semi-structured interviews to further explore mothers’ experiences with the intervention and inform refinements for future research. The study protocol was drafted in accordance with the recommendations of the SPIRIT (Standard Protocol Items: Recommendations for Interventional Trials) statement. The corresponding checklist is available as Supplementary Materials.

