Following completion of T0, mothers will participate in a structured mentalization-based video-feedback program delivered synchronously online over a five-month period, comprising ten fortnightly sessions. During the intervention, mothers will be asked to record brief videos (approximately 5 min) of everyday caregiving interactions with their infant following standardized instructions. Recordings will be shared securely with the clinician and reviewed during online sessions, in which selected interaction sequences will be collaboratively explored to promote maternal reflective functioning and sensitivity (see Section 2.1.7).

Post-intervention assessment (T1) will be completed when infants are approximately 8 months of age, using the same procedures as at baseline. A follow-up assessment (T2) will be conducted when infants are approximately 12 months old to examine the maintenance of effects over time. At both time points, participant feedback will also be collected to explore mothers’ experiences of and satisfaction with the VFI-RF (see Figure 1).

All assessments and intervention sessions will be conducted remotely via secure digital platforms (e.g., Qualtrics, Zoom, Teams), in accordance with data protection and ethical requirements. Clinicians and research staff involved in data collection and observational coding will follow standardized protocols to ensure consistency and reliability across time points and study sites.

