**Figure 2 jcm-15-05271-f002:**
[figure not shown]
Structure and content of the VFI-RF.

**Table 1 jcm-15-05271-t001:** Progression criteria for feasibility and acceptability.

Domain	Area	Indicator	Green	Amber	Red
Feasibility	Enrolment	Mothers referred	≥80% of target	60–79%	<60%
		Eligible among referred	≥60%	40–59%	<40%
		Consented among eligible	≥70%	50–69%	<50%
	Intervention uptake	VFI-RF sessions attended	≥75%	50–74%	<50%
	Retention	Baseline participation	≥90%	75–89%	<75%
		Follow-up participation	≥80%	65–79%	<65%
		Ineligibility/withdrawal reasons across study phases	Infrequent/ non-systematic	Modifiable reasons	Recurrent major issues
	Assessment/data quality	Assessments completed	≥85%	70–84%	<70%
		Missing data on key measures	≤10%	11–20%	>20%
Acceptability	Assessment procedures	Number/frequency acceptable	≥75% positive	50–74%	<50%
		Duration/content/mode acceptable	≥75% positive	50–74%	<50%
	Mothers’ experience	VFI-RF experience	Predominantly positive	Mixed, with modifiable concerns	Predominantly negative or recurrent major concerns
		Satisfaction with VFI-RF/study procedures	≥75% satisfied	50–74%	<50%

**Table 2 jcm-15-05271-t002:** Schedule of participant assessment.

	Pre-Intervention		Post-Intervention	
	Screening	Baseline (T0)	Post-Treatment (T1)	Follow-Up (T2)
Demographics (e.g., age, education, employment and marital status), clinical history, and psychosocial risk variables	✔	✔		
Maternal reflective functioning (PRFQ)		✔	✔	✔
Maternal depression (EPDS)	✔	✔	✔	✔
Maternal anxiety (GAD-7)	✔	✔	✔	✔
Maternal Parenting stress- Short Form (PSI-SF)		✔	✔	✔
Maternal Perceived social support (MSPSS)		✔	✔	✔
Relationship Questionnaire (RQ)		✔		
Maternal postnatal attachment (MPAS)		✔	✔	✔
Child’s emotional and behavioral development (TAPQOL)		✔	✔	✔
Clinical Outcomes in Routine Evaluation- Outcome Measure (CORE-OM)		✔	✔	✔
Satisfaction questionnaire ad hoc			✔	✔

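### Green on consent and retention is read as a definitive trial being feasible, but the single arm never observes consent to randomisation or retention in a comparator

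*Protocol article*

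**What the plan says.** Section 1.4 of the protocol article fixes the design: "This multicenter study is an open-label, single-arm feasibility study using a pre–post design with a nested qualitative evaluation". Section 2.1.6 says what follows baseline: "Following completion of T0, mothers will participate in a structured mentalization-based video-feedback program delivered synchronously online". The article describes no comparator and no allocation procedure.

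Section 1.2 defines the indicators. "Consent rate will be calculated as the proportion of eligible mothers who provide informed consent", and retention is the share of consented mothers who complete each of T0, T1 and T2. In Table 1 the row "Consented among eligible" is green at 70% or more, amber at 50–69% and red below 50%. Follow-up participation is green at 80% or more, amber at 65–79% and red below 65%.

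Section 2.2.1 gives the meaning of the colours: "Green criteria will indicate that progression to a definitive trial is feasible without major modifications". Section 2.3 repeats this reading with the softer verb *suggest*. The last paragraph of 1.3 sets three possible conclusions about the main study, of which the most favourable, (c), is "feasible as originally designed".

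The next study is a randomised trial. The Introduction says feasibility evidence is needed to "optimize the design of a future randomized controlled trial", and 1.3, the Discussion and the Conclusions speak of it in the same terms.

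**The concern.** The primary output of this study is a decision on whether and how to proceed. Consent and retention both feed that decision, and both are observed under a condition the next trial will not share: each mother who agrees knows she will be offered the intervention. Nobody is asked to accept allocation by chance, and nobody is followed without the VFI-RF.

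Adding randomisation and a comparator is a major change between this study and the next. Applied as written, the rule can therefore say that the definitive trial needs no major modification while the features that make it a controlled trial remain untested. Conclusion (c) also has no clear referent, because the only design set out is the single-arm one.

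The Strengths and Limitations section restricts what the single arm can say about effectiveness and about differences between risk profiles. It places no such restriction on what the single arm can say about recruiting to, and retaining mothers in, a randomised trial.

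**Working it through.** **The plan's own figures.** The plan gives none for consent to randomisation or for comparator retention, so there is nothing to reproduce on this point. The sample-size statement in 2.1.4 plays no part in it.

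**Step 1: what Table 1 covers.** There are 13 indicators:
- enrolment: 3 (referred, eligible, consented)
- intervention uptake: 1
- retention: 3 (baseline, follow-up, reasons for ineligibility or withdrawal)
- assessment and data quality: 2
- assessment procedures: 2
- mothers' experience: 2

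None concerns randomisation, a comparator, or follow-up without the intervention. All 13 could be green with no observation on any of these: of the 48 planned mothers, 0 are randomised and 0 are followed in a comparator.

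**Step 2: consent, as an illustration.** Let c be the consent rate seen here and d the share of consenters who would decline if allocation were by chance. Both are assumed. Suppose also that no current decliner would accept randomisation. Consent under randomisation is then c × (1 − d), and it stays green while d ≤ 1 − 0.70/c.

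| c (assumed) | largest d that stays green | d = 10% | d = 20% | d = 30% |
|---|---|---|---|---|
| 70% | 0% | 63.0% amber | 56.0% amber | 49.0% red |
| 75% | 1 − 0.70/0.75 = 6.7% | 67.5% amber | 60.0% amber | 52.5% amber |
| 90% | 1 − 0.70/0.90 = 22.2% | 81.0% green | 72.0% green | 63.0% amber |

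**Step 3: retention, as an illustration.** Let r be follow-up in treated mothers and s the number of percentage points by which a comparator arm falls short. With 1:1 allocation, pooled retention is r − s/2, which stays green while s ≤ 2 × (r − 80).

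| r (assumed) | largest s that stays green | s = 10 | s = 20 |
|---|---|---|---|
| 80% | 0 points | 75% amber | 70% amber |
| 85% | 10 points | 80% green | 75% amber |
| 90% | 20 points | 85% green | 80% green |

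If the comparator arm kept mothers better than the intervention arm, s would be negative and the pooled figure would be higher than r.

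**Step 4: reading the result.** Whether green carries over depends on the margin above the cut-off and on d and s. The study estimates neither d nor s.

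**The case against.** A reader might infer that the rule certifies a randomised trial on two rows alone. The documents do not go that far. Section 2.3 says *suggest*. Section 2.2.1 has numbers and qualitative feedback read together across several criteria. Consent and follow-up are two of 13 unweighted indicators. Section 1.3 also promises to look at obstacles to a later randomised trial and at what amendments or further information it would need. All of this stands and softens the point. It does not remove it, because that exploration has no indicator, question or threshold attached.

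The interview guide and the ad hoc satisfaction questionnaire are not shown, so mothers may in fact be asked about randomisation. That too stands. The point is confined to what Table 1 and the stated meaning of green contain.

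A reader might also infer that the bias runs towards green, since guaranteed treatment is attractive. The documents do not show this. Taking part here also means filming at home, sharing the videos and attending ten sessions. The Introduction treats willingness to record and share as an open question, and the limitations raise privacy and burden. A comparator without those demands could lose fewer mothers. The direction is unknown.

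Finally, a reader might want the overall verdict capped by a willingness-to-be-randomised question. That would rest the decision on a hypothetical answer, and an estimate among all eligible mothers would need data from decliners on a form the article does not describe. The cap is not justified.

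**Conclusion.** The point holds in a limited form. A single-arm study is a legitimate first step; the fault is in the meaning given to green. On the consent and retention rows, green can show that the VFI-RF and its assessments can be recruited to and retained in an intervention arm. It cannot by itself support a definitive randomised trial without major modification, or conclusion (c). This follows from the article's own definitions and does not depend on any assumed figure.

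The size is unknown. On the assumptions above, 75% consent leaves green once more than about 6.7% of consenters would decline randomisation, while 90% consent survives 20% declining. A result just above a cut-off is fragile and a result well above it is not. The data remain usable; what overreaches is the conclusion drawn from them.

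**What to change.** In 1.3, 2.2.1 and 2.3, state three things:
1. Green on the consent and retention rows means that the VFI-RF and its assessments can be recruited to and retained in an intervention arm.
2. These rows do not by themselves support the no-major-modification reading or conclusion (c).
3. Randomisation and comparator retention remain untested and must be tested in a randomised or internal pilot.

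Optionally, ask mothers whether they would have taken part had allocation been by chance, once at the consent approach and once in the T1 feedback already planned. Report the answers descriptively, overall and by risk group, as supporting evidence that does not cap the overall verdict. The consent-stage answer should carry more weight.

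The cost is wording in three sections and, if the option is taken, one question at two contacts. Section 2.1.5 says recruitment has not begun, so on the article's own account this can be settled beforehand. The drawbacks are that stated willingness is an imperfect proxy for behaviour, T1 answers come only from retained, treated mothers, and the headline conclusion becomes narrower.

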#### 2.2.2. Clinical Outcome Measures—Self-Attribution

Parental Reflective Functioning Questionnaire (PRFQ) [4]; Italian version [37]. The PRFQ is an 18-item self-report measure of parental reflective functioning. It comprises three subscales: Interest and Curiosity (IC) (interest in the child’s mental states), Certainty about Mental States (CMS) (tendency toward overly certain/opaque interpretations of the child’s mind), and Pre-Mentalizing (PM) (non-mentalizing or maladaptive attributions about the child’s mental states). Items are rated on a 7-point Likert scale. The Italian validated version will be used and has shown acceptable-to-good internal consistency (PM α = 0.70; CMS α = 0.82; IC α = 0.74).

Edinburgh Postnatal Depression Scale (EPDS) [38] Italian version of [39]. The EPDS is a 10-item self-report screening tool for depressive symptoms in the perinatal period. The Italian validation reported good internal consistency (α = 0.79).

Generalized Anxiety Disorder Scale (GAD-7) [40]; Italian version [41]. The GAD-7 is a 7-item self-report measure assessing symptoms of generalized anxiety. Items are rated on an ordinal response scale, with higher scores indicating greater anxiety symptom severity. A cut-off score of ≥ 10 will be used to indicate probable moderate anxiety.

Parenting Stress Index–Short Form (PSI-SFI) [42] Italian version of [43]. The PSI-SF is a 36-item self-report questionnaire assessing parenting-related stress across three domains: Parental Distress (α = 0.80), Parent–Child Dysfunctional Interaction (α = 0.81), and Difficult Child (α = 0.72). Items are rated on a Likert scale, and a total parenting stress score can be derived (α = 0.89).

Multidimensional Scale of Perceived Social Support (MSPSS) [44]; Italian version [45]. The MSPSS is a 12-item self-report measure assessing perceived social support from Family, Friends, and a Significant Other. Items are rated on a 7-point Likert scale, with higher scores indicating greater perceived support. The Italian version demonstrates adequate reliability comparable to the original scale, with Cronbach’s α ranging from 0.87 to 0.91.

Relationship Questionnaire (RQ) [46]; Italian version [47]. The RQ is a single-item measure designed to evaluate adult attachment style. Respondents are presented with four short paragraphs describing prototypical attachment patterns—secure, fearful, preoccupied, and dismissing—and are asked to select the description that best represents their typical approach to close relationships.

Maternal Postnatal Attachment Scale (MPAS) ([48]; Italian version [49]). The MPAS is a 19-item self-report measure assessing the mother’s emotional bond with her infant in the postnatal period, including dimensions such as quality of attachment, absence of hostility, and pleasure in interaction. The Italian validation reported good internal consistency (α = 0.77).

TNO-AZL Preschool Children Quality of Life (TAPQOL) [50]. The TAPQOL is a 43-item parent-report questionnaire assessing health-related quality of life in young children (approximately 9 months to 6 years), covering multiple domains (e.g., sleep, mood, anxiety, problem behavior).

Clinical Outcomes in Routine Evaluation—Outcome Measure (CORE-OM) ([51]; Italian version [52]). The CORE-OM is a 34-item self-report measure of adult psychological distress and functioning, developed to monitor change over the course of psychological treatment. The Italian validation reported good internal consistency (α = 0.90) for the total score.

The timeline and the specific timing of each psychological assessment across the study waves are detailed in Table 2.

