### 2.3. Data Analysis

Analyses will first focus on the primary feasibility and acceptability outcomes. Recruitment, eligibility, consent, intervention uptake, retention, assessment completion, missing data, and participant-reported acceptability will be summarized descriptively and evaluated against the pre-specified traffic-light progression criteria reported in Table 1. Indicators falling within the green range will suggest that progression to a future definitive trial is feasible without major modifications; amber indicators will suggest that progression may be feasible following protocol refinements; and red indicators will indicate that substantial modifications or redesign would be required before proceeding. Quantitative feasibility indicators will be interpreted together with qualitative feedback from participants and service providers to provide an integrated assessment of the feasibility and acceptability of the VFI-RF intervention and study procedures.

Exploratory analyses of secondary outcomes will examine changes from baseline (T0) to post-intervention (T1) and follow-up (T2). Linear mixed-effects models for repeated measures will be fitted separately for each secondary outcome, including assessment time as the main within-subject factor of interest. Maternal–infant risk profile will be included to account for heterogeneity in the sample and will be defined according to the presence of infant preterm birth, clinically significant anxiety and/or depressive symptoms, or the co-occurrence of psychosocial and infant-related risk factors.

The primary exploratory focus of these models will be on the effect of time, describing whether outcome scores change across assessment points, and on the time × risk profile interaction, exploring whether trajectories of change differ across risk subgroups. The main effect of risk profile will be considered only as an adjustment factor and descriptive indicator of baseline/sample heterogeneity, rather than as a primary inferential target.

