Planned exploratory contrasts will estimate changes from T0 to T1 and from T0 to T2. Where appropriate, T1 to T2 contrasts will also be examined to describe whether observed changes appear to be maintained, reduced, or further increased over time. Effect estimates, confidence intervals, and descriptive patterns of observed change will be reported. Given the feasibility nature of the study, the expected small sample size, and the absence of a comparison group, all analyses of secondary outcomes will be interpreted cautiously as exploratory and hypothesis-generating only, and will not be considered definitive evidence of intervention effectiveness.

All statistical analyses will be conducted using SPSS Statistics version 30.0 (IBM Corp., Armonk, NY, USA).

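### TAPQOL is scheduled clearly below its stated age range at T0 and marginally below it at T1, so no planned child quality-of-life contrast has both waves in range

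*Protocol article*

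**What the plan says.** Section 2.2.2 describes the instrument: "The TAPQOL is a 43-item parent-report questionnaire assessing health-related quality of life in young children (approximately 9 months to 6 years"). Section 1.4 fixes the three assessments at "baseline (T0; infant age ~3 months), post-intervention (T1; infant age ~8 months), and follow-up (T2; infant age ~12 months"). Section 2.1.6 repeats the later two ages: "Post-intervention assessment (T1) will be completed when infants are approximately 8 months of age, using the same procedures as at baseline", and "A follow-up assessment (T2) will be conducted when infants are approximately 12 months old".

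In Table 2 the row "Child’s emotional and behavioral development (TAPQOL") is ticked at T0, T1 and T2. Section 1.3 makes the construct a secondary exploratory outcome whose trajectory is to be described, listing "maternal emotional bonding with the infant, and health-related quality of life in young children". Section 2.3 applies one analysis to all such outcomes: "Linear mixed-effects models for repeated measures will be fitted separately for each secondary outcome", with time as the within-subject factor. It continues: "Planned exploratory contrasts will estimate changes from T0 to T1 and from T0 to T2". A T1 to T2 contrast is added only where it is judged suitable. The Discussion and Conclusions again list child health-related quality of life among the trajectories to be described.

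Nothing in the article exempts TAPQOL from the T0 or T1 assessment, names a version for younger infants, or gives a reason for using it below the stated age.

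**The concern.** A change score needs an instrument that applies at both ends of the interval. If a parent completes a questionnaire for an infant well below the age it is meant for, a later difference may show only that the items have become applicable as the child grew. In a single-arm study there is no comparison group in which the same artefact would appear and cancel.

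Two things are at stake. First, Section 1.3 says the secondary outcomes are there to judge whether the measures are suitable and sensitive enough for a later controlled trial. Flat or erratic TAPQOL scores, or poor completion, could not be separated from use at the wrong age. Second, Section 1.2 counts completion of the planned questionnaires at each wave, and Table 1 asks whether assessment content and duration are acceptable. A long questionnaire that does not suit the infant's age adds burden to those primary indicators.

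**Working it through.** No sample-size, power or alpha figure is involved. The check sets the protocol's own ages against its own range.

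**Inputs**
- TAPQOL range (Section 2.2.2): about 9 months to 6 years, that is 9 to 72 months.
- Infant age (Sections 1.4 and 2.1.6): T0 about 3 months, T1 about 8, T2 about 12.
- TAPQOL waves (Table 2): T0, T1, T2.
- Contrasts (Section 2.3): T0 to T1, T0 to T2, and optionally T1 to T2.

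**Step 1. Each wave against the lower limit** (shortfall = 9 − age)

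| Wave | Age (months) | Shortfall | Status |
|---|---|---|---|
| T0 | 3 | 9 − 3 = 6 | clearly below |
| T1 | 8 | 9 − 8 = 1 | marginally below |
| T2 | 12 | none | in range |

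**Step 2. Each contrast**

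| Contrast | Waves below range | Reading |
|---|---|---|
| T0 to T1 | T0 and T1 | not interpretable as change |
| T0 to T2 | T0 | not interpretable as change |
| T1 to T2 (optional) | T1, by about 1 month | borderline |

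**Step 3. Could the session calendar bring T1 into range?** Ten fortnightly sessions span nine intervals: 3 + 9 × 14 / 30.4375 = 7.1 months. Allowing ten intervals gives 3 + 10 × 14 / 30.4375 = 7.6 months. Neither reaches 9.

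**Step 4. Preterm infants.** The article does not say whether ages are chronological or corrected. Suppose corrected age were used, taking term as 40 weeks and births at 28 to 36 weeks (my assumptions). Corrected age is age − (40 − gestational weeks) × 7 / 30.4375.
- T0: 0.2 to 2.1 months.
- T1: 5.2 to 7.1 months.
- T2: 9.2 to 11.1 months.

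This widens the shortfall at T0 and T1 and leaves T2 in range.

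**Step 5. Item load.** Item counts from Section 2.2.2, for the scales ticked at T0 (RQ counted as one item): PRFQ 18 + EPDS 10 + GAD-7 7 + PSI-SF 36 + MSPSS 12 + RQ 1 + MPAS 19 + TAPQOL 43 + CORE-OM 34 = 180. RQ is not repeated, so T1 has 179.
- T0: 43 / 180 = 23.9%.
- T1: 43 / 179 = 24.0%.

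These shares cover the named scales only. Table 2 also schedules demographic, clinical-history and psychosocial items at T0 and an ad hoc satisfaction questionnaire at T1, with no item counts, so the share of the whole battery is lower by an unknown amount.

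**Step 6. Other text on T0.** The list of baseline measures in Section 2.1.6 does not mention child quality of life, whereas Table 2 does. That list also leaves out maternal bonding, which Table 2 ticks at T0. It therefore reads as a summary rather than a deliberate exclusion of TAPQOL, but the two places should be made to agree.

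**The case against.** The best defence is that the ages and the limit are all approximate. An infant of about 8 months and a floor of about 9 months differ by little, and the T1 to T2 contrast is optional. That stands. A reader might infer that every TAPQOL change estimate is invalid; the documents do not support so flat a statement for T1 to T2. Approximation does not rescue T0, however, where the infant is at one third of the minimum age, and both main contrasts start from T0.

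A second defence is that everything here is exploratory, the study disclaims efficacy, and no Table 1 criterion uses a TAPQOL score. This also stands and limits the severity. It does not remove the contradiction, because suitability of the measures is itself a stated aim.

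A reader might also project a missing-data rate from the T0 and T1 administrations and set it against the green limit of 10% or less. The documents do not support that. They do not say how many mothers would leave items blank, which measures count as key, or whether missingness is counted by item or by scale. Some listed domains, such as sleep and mood, can be reported for a young infant, so the answers could be complete but hard to interpret.

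Finally, lower acceptability caused by an ill-fitting questionnaire could be called a finding that a feasibility study is meant to deliver. That is fair: it is not a bias in the feasibility result. It is an avoidable one, since the mismatch can be seen before the first mother is enrolled.

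**Conclusion.** The protocol contradicts itself and should be corrected. By its own range, TAPQOL is out of range at two of three waves: by about 6 months at T0 and about 1 month at T1. None of the three possible contrasts has both waves in range. T0 to T1 and T0 to T2 cannot be read as change in child health-related quality of life; T1 to T2 is borderline; the T2 score stands on its own.

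The effect on the primary indicators is 43 extra items at each of T0 and T1 and a possible loss of completion and acceptability whose size cannot be stated.

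The conclusion rests on taking the stated age range and the stated infant ages at face value, and on the absence of any text naming a version for younger infants. It concerns one secondary exploratory outcome, so it is a should-fix point and leaves the feasibility design intact.

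**What to change.** Reconcile Section 2.2.2 with Table 2 before recruitment, since a T0 score collected at about 3 months cannot be repaired afterwards. The article states that recruitment had not begun. Either of two routes is sound.

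1. **Keep TAPQOL at T2 only.** Remove the T0 and T1 ticks in Table 2. State in Section 2.3 that TAPQOL is outside the repeated-measures models and contrasts, and that the T2 score will be reported descriptively, overall and by risk group. Amend Section 1.3, the Discussion and the Conclusions so that they no longer promise a child quality-of-life trajectory. Cost: text edits, and no child quality-of-life change score, although the stated age range does not support the planned one. Gain: 43 fewer items at each of T0 and T1.

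2. **Keep the trajectory and change the instrument.** Replace TAPQOL with a measure whose stated range covers about 3, 8 and 12 months, and leave the models and contrasts as they are. Cost: choosing and justifying a new measure, including its Italian version, and updating Section 2.2.2 and Table 2.

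Under either route, align the baseline list in Section 2.1.6 with Table 2, and make the Table 2 row label, which speaks of emotional and behavioral development, match the quality-of-life construct in Sections 1.3 and 2.2.2.
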